### Random allocation procedures

Randomization will be performed using a random permutated block design. The allocation will be performed using a random number generator. Three persons will be assigned to each block. The first person in the block will have an equal probability of being randomized into any of the three conditions. The second person will be randomized into one of the two remaining conditions and the third person in the block will automatically be placed into the third condition that has not been assigned.

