### Sample size

In order to achieve an adequate power of 0.80 to test hypotheses, we will seek to recruit a total of 189 individuals for this study and, more specifically, 63 in each condition. The total number of individuals to be recruited is based on calculations of sample size and power for a balanced repeated-measure mixed effect model with three time points (Weeks 1, 12, and 24) using a formula provided by Hedeker et al.
[33]. We assumed equal variance and correlation (rho = 0.5) between measures across time points, and an effect size of 0.6 at Weeks 12 and 24. These calculations account for 20% attrition over time.

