### Recruitment and eligibility

Individuals for this study will be recruited in several different ways in the State of Ohio. We have restricted recruitment to Ohio to avoid complications with state licensure laws. Fliers for the study will be distributed through MS support groups and National MS Society and MS Association of America events. We will recruit through physician referral and electronic health record review, and an MS patient registry maintained by the North American Research Consortium on MS (NARCOMS), which has approximately 400 registered individuals in Ohio who are ambulatory. Regardless of the recruitment method, individuals who are interested in participating in the study will be asked to contact the study office. Potential participants will undergo a telephone screening procedure to determine eligibility, and then a confirmation of eligibility through contacting their physician.

Inclusion criteria are: (1) physician-confirmed diagnosis of MS and physician-consent to initiate a physical activity program, (2) age between 18 and 65 years, (3) ability to walk at least 25 feet with a cane, (4) ability to carry on telephone conservations in English, (5) a Patient Determined Disease Step score between 1 (mild disability) and 5 (unilateral support required)
[34], (6) a current sedentary lifestyle (i.e., purposeful exercises ≤ 2 days per week for 30 minutes)
[35], and (7) experiences moderate to severe fatigue (a score of ≥ 4 on the Fatigue Severity Scale)
[36]. Exclusion criteria are: (1) pregnancy, (2) cardiopulmonary diseases, (3) uncontrolled diabetes (hospitalized within the last six months), (4) greater than three falls in the past six months, and (5) severe cognitive deficits (weighted score of less than 12 on the short version of the Blessed Orientation Memory Concentration test)
[37].

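### A single stated block size of three makes every third allocation certain to anyone who knows the earlier assignments in order; hidden, varying block sizes would remove most of that certainty

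*Protocol article*

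**What the plan says.** The protocol article, under Random allocation procedures, sets out the whole block mechanism:

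- Method: "Randomization will be performed using a random permutated block design", with "The allocation will be performed using a random number generator".
- Block size: "Three persons will be assigned to each block". No other size and no stratification are described.
- First place: "The first person in the block will have an equal probability of being randomized into any of the three conditions".
- Second place: "The second person will be randomized into one of the two remaining conditions".
- Third place: "the third person in the block will automatically be placed into the third condition that has not been assigned".

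Under Sample size the article gives the target: "we will seek to recruit a total of 189 individuals for this study and, more specifically, 63 in each condition".

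On entry to the trial, Recruitment and eligibility says that interested people contact the study office. Then "Potential participants will undergo a telephone screening procedure to determine eligibility", and the physician confirms eligibility. Intervention procedures shows that the arms differ in content, and that the physical activity-only arm has three teleconferences against six in the other two. The therapist and the assistants who make the calls therefore know who is in which arm.

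**The concern.** Three is the smallest block that can hold a 1:1:1 allocation, so it is the most predictable permuted block available. The size is constant and only one sequence is described, so counting from the first participant gives each person's place in the block. Someone who also knows the assignments so far knows the next arm outright one time in three.

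If that person could also influence who enters next, or when, the arms could come to differ in ways that randomisation is meant to prevent. An entrant thought more likely to take up physical activity could be timed into one arm. That would affect accelerometer results as much as questionnaires, so it bears on all three primary outcomes.

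**Working it through.** **Inputs.** N = 189 and 63 per condition (Sample size). Block size 3, with the first place open to three arms, the second to two and the third to one (Random allocation procedures). An equal split at the second place is implied by a permuted block, though no probability is stated for it.

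**Plan's own figure.** 189 / 3 = 63 complete blocks with one person per arm in each, which gives 63 per arm. This matches the target exactly.

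**Predictability of the stated scheme.** Take an observer who knows all earlier assignments in order and always names the most likely arm.

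- Chance of being right by place in the block: 1/3, 1/2, 1.
- Expected correct guesses per block: 1/3 + 1/2 + 1 = 11/6.
- Best-guess rate: (11/6) / 3 = 61.1%, or 0.611 × 189 = 115.5 allocations.
- Certain allocations: 63 of 189 (33.3%).
- Allocations where at least one arm is excluded: 63 + 63 = 126 of 189 (66.7%).

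**Alternatives, same observer.** Fixed sizes are exact. Varying sizes are simulated (150 simulated trials of 189), with the observer knowing which sizes are possible but not their order.

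| Scheme | Best-guess rate | Certain allocations of 189 |
|---|---|---|
| Fixed 3 (as stated) | 61.1% | 63 |
| Fixed 6 | 56.1% | 37.8 |
| Fixed 9 | 53.2% | 27 |
| Random 3/6 | about 57.7% | about 17 |
| Random 3/6/9 | about 55.5% | about 7 |
| Random 6/9 | about 54.3% | about 10 |
| Random 6/9/12 | about 52.7% | about 4 |
| Simple randomisation | 33.3% | 0 |

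**What the change gains.** With random 3/6/9, certain allocations fall by about 63 − 7 = 56. The best-guess rate falls by only 61.1 − 55.5 = 5.6 percentage points. Simple randomisation is the wrong yardstick for this gain, because it is not the proposed change and would give up the balance that blocking provides.

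**What it costs in balance.** If recruitment stops mid-block, two arms can differ by at most 1 with blocks of three. With a block of nine, which holds three places per arm, they can differ by at most 3.

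**The case against.** The strongest reply is that predictability harms the trial only if those who screen and enrol see the earlier assignments in order. The article assigns screening to the study office and delivery to a therapist and an assistant. It does not say that these roles overlap, who holds the sequence, or when an assignment is released. Such details are commonly left to the full protocol, so their absence is no fault here. Self-referral and confirmation by the participant's own physician also limit staff control over timing, without removing it. This objection stands: a reader might infer that staff will see and steer allocations, and the documents do not support that.

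A second reply is that the analysis offers some protection. The Fatigue Impact Scale is measured at baseline, baseline differences become covariates (Data management and analysis), and potential control variables are collected (Secondary dependent variables). This stands in part. It would be too strong to say that no analysis could help. But motivation is not among the listed control variables. The baseline psychosocial scales, such as exercise self-efficacy, may capture some of it but not all.

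A reader might also argue that self-reported primary outcomes make the problem worse. That does not follow, since self-report bears on reporting bias and not on who enters which arm.

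Finally, permuted blocks of three are a recognised design that gives exact balance, and the numbers agree with the sample size section. That is true. The point is a weak choice, not an internal error.

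**Conclusion.** The point holds as a weakness in a stated rule. Fixed blocks of three make 63 of 189 allocations certain, and the best-guess rate 61%, for anyone who knows the earlier assignments in order. The 61% is a ceiling: it assumes the full ordered history, one unstratified sequence and optimal guessing.

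Selection bias is a conditional risk. The documents neither establish nor exclude the condition that recruiting staff know earlier assignments, and nothing in them shows that enrolment would be steered. If it were, baseline adjustment could reduce the bias but not fully remove it for unmeasured traits. This is a low-cost improvement to the design; it does not invalidate the trial.

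**What to change.** Under Random allocation procedures, replace the sentence fixing three persons per block, and the description of the automatic third placement, with wording such as: allocation follows a computer-generated list of permuted blocks whose sizes (for example 3, 6 and 9) are in random order and are not disclosed to recruiting staff. In practice the actual sizes belong in a restricted document.

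The cost is a regenerated list and one revised paragraph, with no change to sample size. The downside is the small imbalance shown above if recruitment ends mid-block. Because a best-guess rate of about 55% remains, the change supplements concealment of the sequence from those who enrol and does not replace it. If the full protocol already provides that concealment, a cross-reference would be enough on that side.

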### Intervention procedures

#### Physical activity-only intervention

This intervention will consist of three group teleconference sessions and four one-to-one calls. The overall purpose of the group teleconferencing will be to teach people how to engage in physical activity and set personalized goals to increase physical activity. The overall purpose of the one-to-one telephone calls will be to provide feedback and encouragement on achieving physical activity goals. Participants will first receive the three one-hour weekly group teleconference sessions from a licensed occupational therapist (OT). We selected OTs to deliver the teleconference sessions because of their expertise and training in managing group processes to facilitate behavior change. Participants will also be provided with four 10 to 20-minute, one-to-one, structured, follow-up telephone calls with a graduate assistant every other week. Both the group teleconference sessions and one-to-one follow-up telephone calls will be consistent with goal-setting theory
[38] and increasing self-efficacy using verbal persuasion, teaching how to set measurable and reasonable goals, proving feedback on goals, and using role modeling (e.g., group members sharing stories)
[39].

The first intervention session will focus on discussing the safety precautions for and benefits of physical activity specifically for persons with MS, and then teaching participants how to use a pedometer to monitor physical activity levels. Homework will be assigned to self-monitor walking behavior using the pedometer to generate a baseline level of physical activity for subsequent goal-setting. The second session will focus on using the pedometer to set goals. Participants will be encouraged to achieve personal goals related to the accumulation of pedometer steps by at least 1% every week. Participants will have the option to set additional goals related to exercise, which they can keep track of in their exercise log. Homework will be assigned to set personalized physical activity goals. The final session will focus on the personalized goals, and feedback from the OT and other group members on the appropriateness of goals. There will be a discussion and summary of the guiding principles that will help persons with MS safely engage in physical activity and overcoming barriers to engagement. The one-to-one follow-up telephone calls will focus on providing feedback on physical activity goals. Goals will be reviewed and adjusted biweekly under the guidance of a trained research assistant. The aim will be to teach the participant how to set and adjust goals independently.

#### FM+ intervention

Participants randomized into this intervention will first receive the three goal-setting physical activity teleconference sessions with the OT, and then will receive three additional teleconference sessions on fatigue management principles with the same OT. Thus, participants will receive a total of six group teleconference sessions. The participants will start to receive the four one-to-one calls from the research assistant after the completion of the first three session. For the purpose of this study, we will only teach fatigue management principles that can be integrated into the focus of changing physical activity behavior. This will include topics emphasizing the importance of rest throughout the day, setting priorities, activity analysis and modification, and living a balanced lifestyle. The first FM+ session will focus on teaching the guiding principles of fatigue management, and discussing the fatigue cycle and how inactivity and deconditioning can make fatigue worse. The second FM + section will focus on evaluating priorities, making active decisions, and using rest strategically in order to have adequate energy to engage in physical activity. The third FM + session will focus on teaching participants how to analyze and modify their schedules in order to manage their fatigue and achieve physical activity goals.

#### Contact-control social support intervention

The contact control group will consist of the same number of contacts as the FM+, i.e., six weekly one-hour teleconference calls with four biweekly one-to-one phone calls. Thus, this condition will allow us to determine whether it is the actual content being taught in the goal-setting physical activity intervention and FM+ intervention that is beneficial, rather than simply the contacts with the OT or social support provided by other group members. The teleconference calls and the one-to-one calls will involve a discussion of topics commonly addressed in support groups. Topics will include information on MS, disease modifying medications, preventive screening, community organizations, nutrition and supplements, cognitive problems, and recognizing symptoms of depression and chronic stress. For the teleconference sessions, participants will be given the opportunity to share problems and provide peer support and solutions for others. For the one-to-one calls, participants will be asked about topics of interest, and the graduate student will gather educational materials and send them to the participant. This information will be the basis for the discussion in the calls. When issues related to fatigue and physical activity are raised, participants will be directed to publically available educational pamphlets. This type of social support group has been used successfully in other clinical trials as a control condition to evaluate the efficacy of fatigue management programs in persons with MS
[40].

##### Ensuring the fidelity of the interventions

Guidelines suggested by Bellg
[41] will be implemented to promote uniform application of all three interventions. For example, a manual of operating procedures will be provided to interventionists and incorporated into training. Interventionists’ adherence to the intervention protocol will be verified using a checklist and episodic monitoring of the sessions over the phone. Fidelity of the intervention “dose” will be further monitored by tracking attendance for each session, monitoring the completion of worksheets, and testing comprehension.

##### Primary dependent variables

All dependent variables will be administered at baseline, at the end of the 12-week intervention period, and at a 24-week follow-up period through the mail.

Fatigue impact will be measured using the Fatigue Impact Scale
[27]. This 40-item scale evaluates the perceived impact of fatigue on everyday life, and is valid and reliable among people with MS. It was developed by interviewing patients with MS, and has discriminant validity between patients with MS, general fatigue, and essential hypertension
[27]. Respondents rate each statement using a five-point Likert-type scale ranging from 0 (no problem) to 4 (extreme problem). A total score and three subscale scores (physical, social, cognitive) can be produced from participants responses. The FIS was used to detect changes in fatigue impact resulting from a fatigue management teleconference program
[10].

Physical activity will be evaluated using the Godin Leisure-Time Exercise Questionnaire (GLTEQ)
[28] and an Actigraph tri-axis accelerometer. The GLTEQ is a self-administered measure of usual physical activity. The GLTEQ includes three items that measure the frequency of strenuous, moderate, and mild exercise for periods of more than 15 minutes during one’s free time in a typical week. Participants will be sent an accelerometer to wear daily over three seven-day periods (baseline, post-test, and follow-up). Data are retrieved for analysis via a computer and software provided with the unit. We will use an epoch of one minute. Participants will be instructed to wear the accelerometers all day, except while showering and swimming, for each of the three seven-day measurement periods. The participant will use a log to record the time that the accelerometer is worn, and this will be verified by inspection of the minute-by-minute accelerometer data. Motl et al. have demonstrated the validity and reliability of both the GLTEQ and the accelerometer in the population with MS
[42].

##### Secondary dependent variables

Health-related quality of life, mental health, and participation in life roles will be measured with the SF-12, Mental Health Inventory, and Community Participation Indicator (CPI), respectively. The SF-12 and Mental Health Inventory are valid and reliable measures, and are commonly used in the population with MS
[43]. The CPI is a new measure developed by Heinemann and colleagues. The measure was developed with input from multiple stakeholders, and has been validated through Rasch analysis in a sample of 1,163 individuals with a variety of disabling conditions
[31,32]. In a subsequent online survey study, the measure had good test-retest reliability over a 2.5 month period in people with MS (t = 0.12, p = 0.91; r = 0.84, p < 0.01). For each item, respondents rate the frequency of engagement (either in days, hours, or times per week, depending on the type of activity), whether it was important (yes/no), and whether they were doing it not enough, enough, or too much. Examples of the 20 items included are: work for money, provide care for a loved one, volunteer, and participate in learning activities.

Six questionnaires will be implemented to identify underlying mechanisms of the interventions’ possible effectiveness for increasing physical activity levels and reducing fatigue impact. Psychosocial construct measures for physical activity will be the Self-Efficacy for Exercise Scale
[44], Exercise Goal-Setting Scale
[12,45], and Multidimensional Outcome Expectations Scale
[46]. All three questionnaires are validated and have been used in previous MS research on physical activity
[45,47]. Psychosocial construct measures for fatigue management will be the validated Self-Efficacy for Performing Energy Conservation Strategies
[48] along with two additional measures on goal-setting and outcome expectations, which will be developed and validated during the study.

To address potential confounders on the interventions’ effects, information will be collected from participants for the purposes of post-hoc sub-group comparisons and potential use as control variables. These variables will include age, sex, educational level, medications, exacerbations, functional level, and involvement in any other wellness, rehabilitation, or exercise program. Information about changes in MS-related disability, exacerbations, medications, use of rehabilitation programs and other types of exercise/educational programs, and reasons for attrition will be gathered over the phone at 12 weeks and at the 24-week follow-up.

##### Data management and analysis

A secure online application, Research Electronic Data Capture
[49], will be used to manage recruitment efforts and facilitate data collection. The first step in the analysis process will be to compute summary statistics, calculate outcome scores, and conduct quality control assessments. The second step in the analysis will be to test whether the randomization process resulted in equivalent groups at baseline. If differences are found at baseline, these variables will be used as covariates during the hypothesis testing phase. The third step in the analysis process will be addressing normality assumptions, and the potential for missing data, before hypothesis testing begins. If the normality assumption is violated, then an appropriate data transformation will be used. Missing data will be treated conservatively. If appropriate, maximum likelihood, multiple imputation, or last observation carried forward will be used to estimate the missing values. After addressing issues of attrition and missing data, the fourth step will be to conduct intent-to-treat analysis to test the hypotheses. Linear mixed-effects models will be used as the primary analysis tool for testing hypotheses, which include condition, time, and interactions as the fixed covariates, and a random intercept that models the correlation among outcomes collected from the same subject. The mixed models will allow us to determine whether there are significant differences between the three conditions and whether there are significant differences across time. All tests will be two-sided, and p = 0.05 will serve as the criterion for significance. As is typically the case for mixed-effects analyses, the results will not be controlled for multiple comparisons. The generalized estimating equation approaches will be used if the normality distributional assumption is violated for the random effects in the mixed models. To test for mediation, we will use a linear regression model. This analysis will first involve regressing changes in fatigue impact or physical activity on the intervention conditions, and then regressing changes in fatigue or physical activity on the intervention conditions plus changes in the potential mediator. Mediation will be based on the interventions’ association with physical activity or fatigue impact being reduced in magnitude and non-significant after controlling for the mediator variable.

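### Covariates are chosen by testing for baseline differences, a rule that gives the condition-by-time contrast almost no protection, while the Week 1 outcome is used less efficiently than it could be

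*Protocol article*

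**What the plan says.** In the Protocol article, Data management and analysis, the second analysis step is to "test whether the randomization process resulted in equivalent groups at baseline". The rule that follows is: "If differences are found at baseline, these variables will be used as covariates during the hypothesis testing phase". The primary tool is a linear mixed model with fixed effects "which include condition, time, and interactions as the fixed covariates", and "a random intercept that models the correlation among outcomes collected from the same subject". Sample size describes a "balanced repeated-measure mixed effect model with three time points (Weeks 1, 12, and 24"), so the Week 1 outcome is one of the modelled responses and, with a condition main effect in the model, each arm has its own Week 1 mean.

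Under Secondary dependent variables, a list of seven participant characteristics is collected "for the purposes of post-hoc sub-group comparisons and potential use as control variables". It includes medications, exacerbations and involvement in other exercise or rehabilitation programmes, and it is not limited to baseline values. The next sentence adds that "Information about changes in MS-related disability, exacerbations, medications, use of rehabilitation programs and other types of exercise/educational programs" will be recorded at 12 and 24 weeks.

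**The concern.** Random allocation procedures describes permuted blocks of three, so any baseline difference between arms is due to chance. A test of equivalence therefore has no hypothesis left to examine. Using its result to choose covariates favours variables that happen to be unbalanced over variables that predict outcome, and the primary model is not known until the data are seen.

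There is a second problem. The hypotheses concern improvement from baseline, which in this model is the condition-by-time contrast. A fixed subject-level covariate largely cancels out of that contrast, so the rule does little of what a reader would take it to do. Meanwhile the variable most likely to predict the outcome, its own Week 1 value, enters with a free mean per arm, which gives up precision that the collected data could supply.

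Third, the wording on control variables leaves room for adjusting for events after randomisation. Joining an exercise programme, for example, could be a consequence of the physical-activity arms, and adjusting for it would remove part of the effect being estimated.

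**Working it through.** **Inputs.** From Sample size: 63 per arm, rho = 0.5 with equal variances, effect size 0.6 at Weeks 12 and 24, power 0.80, 20% attrition. From Data management and analysis: two-sided 0.05 and the model above. Outcomes are on the standardised scale (SD = 1).

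**The plan's own figure.** A two-group comparison at 0.6 SD needs 2 × (1.96 + 0.84)² / 0.6² = 43.6, so 44 completers per arm and 44 / 0.8 = 55 recruited. This does not reproduce 63. The cited formula is not shown, and 63 follows under some inputs the article does not state (such as power 0.85: 50 completers, 63 recruited), so 63 is not shown to be wrong. It has no bearing on this point beyond supplying 63 × 0.8 ≈ 50 completers per arm.

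**1. How often the rule would fire by chance.** With k independent variables tested at 0.05, the chance of at least one flag is 1 − 0.95^k. For k = 7 this is 30%; for k = 12 it is 46%. The counts and the independence are assumptions.

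**2. What a flagged covariate does to the contrast.** With complete data the contrast at Week 12 is (arm A mean at Week 12 − at Week 1) − (the same for arm B). A time-constant covariate contributes equally to both terms of each within-person difference and cancels. Fits to simulated data (63 per arm, rho = 0.5, covariate correlated 0.4 with the outcome, an assumption) agree:

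| Setting | Shift in condition-by-time estimate | Standard error |
|---|---|---|
| Complete data, covariate as main effect | about 10⁻¹⁴ at most | ratio 1.000 |
| Complete data, baseline outcome as covariate | about 10⁻¹⁴ at most | ratio 1.000 |
| 20% random dropout, likelihood fit | mean 0.012 SD, maximum 0.049 | about 0.185, ratio 0.998 |
| Complete data, covariate crossed with time | mean about 0.009 SD | not tabulated |

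A second set of fits with dropout gave a mean shift of 0.009 SD and a maximum of 0.024, against a standard error of 0.186. The coefficient for condition itself, which here is the Week 1 arm difference, moved by about 0.058 SD.

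**3. Cost of free baseline means.** Per-person variance of the single-time contrast:
- free means (raw change): 2(1 − rho) = 2 × 0.5 = 1.00
- constrained means, or conditioning on baseline: 1 − rho² = 1 − 0.25 = 0.75

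The ratio is (1 + rho)/2, a saving of 35%, 25% and 15% at rho = 0.3, 0.5 and 0.7. With 50 completers per arm the standard errors are √(2 × 1.00/50) = 0.200 and √(2 × 0.75/50) = 0.173. Power for 0.6 is then Φ(0.6/0.200 − 1.96) = Φ(1.04) = 0.851 and Φ(0.6/0.173 − 1.96) = Φ(1.50) = 0.934. Completers needed for 80% power fall from 44 to 33 per arm. Simulated mean standard errors were 0.179 against 0.155 (complete data) and 0.185 against 0.162 (20% dropout).

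**4. Carry-over of chance imbalance.** The largest imbalance a 0.05 test would miss is 1.96 × √(2/63) = 0.35 SD, which carries (1 − 0.5) × 0.35 = 0.17 SD into the change contrast. That is the extreme. Among non-significant imbalances the mean absolute size is about 0.128 SD, carrying 0.064 SD. This is not a further cost beyond step 3: 1.00 − 0.75 = 0.25 = (1 − rho)², exactly the variance that chance imbalance contributes.

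**The case against.** **The cancellation has limits.** It is exact only with complete or imputed data and a time-constant main effect. The article does not rule out covariate-by-time terms, it plans for attrition, and it also speaks of differences between conditions, a comparison that a covariate can move. This stands, so a reader should not infer that the rule corrects nothing at all. But the shifts found are small beside the standard error, and the hypotheses are about improvement. The simulations drew dropout at random and gave the covariate an effect constant over time, so they do not cover dropout related to the covariate.

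**The two complaints pull against each other.** If covariates barely move the contrast, choosing them badly barely harms it. That is fair. The case against the rule is that it gives a data-dependent model and almost no protection in return, not that it distorts the result.

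**Free baseline means are a standard, valid analysis.** Agreed. A reader might infer a biased contrast or an underpowered trial. Neither is supported: the contrast is unbiased over repeated randomisation, the 0.17 SD figure is a conditional worst case, and power at 50 completers is about 0.85, above the stated 0.80.

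**Adjustment for post-randomisation variables is not stated.** A reader might infer that the 12- and 24-week changes will enter the model. The documents do not say so: the listed variables could be used at their baseline values, and the only covariate rule in the analysis section concerns baseline differences. The wording permits such adjustment without committing to it, so the request is for a restriction.

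**An unseen analysis plan may settle the details.** It may, but the testing rule is stated in the article, not left out of it.

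**Conclusion.** The point holds in a limited form. The article states a rule that selects covariates by chance imbalance, and in its own model that rule leaves the main contrast exactly unchanged (complete data, time-constant covariate) or moved by about 0.01 SD against a standard error of about 0.19 (20% random dropout). Separately, leaving baseline means free gives up a quarter of the contrast variance at the plan's rho, worth power of 0.93 instead of 0.85 for an effect of 0.6. This is a loss of efficiency, not an invalid analysis or a missed power target. The figures rest on rho = 0.5, equal variances, about 50 completers per arm and dropout unrelated to outcome or covariates. On control variables, the finding is an ambiguity to be closed.

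**What to change.** In Data management and analysis:
- Delete the baseline equivalence tests and the conditional covariate rule. Baseline characteristics can be tabulated without tests.
- Keep Week 1 in the response but constrain arm means to be equal there: time effects plus condition effects at Weeks 12 and 24 only, with no condition main effect. Conditioning on the baseline outcome is an acceptable alternative.
- Name in advance a short set of pre-randomisation covariates, chosen for expected prognostic value, each interacted with time. Disease Step score, age and sex are candidates, although the article gives no evidence on their prognostic strength.

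Under Secondary dependent variables, limit control variables to values before randomisation, and report later exacerbations, medication changes and outside programmes descriptively.

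The cost is minor rewording, and all the data are already to be collected. The one condition is that Week 1 measures are taken before any intervention exposure. Primary dependent variables calls them baseline, which implies this, but the timing should be stated explicitly before the constraint is adopted.
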